### Drop-outs

Participants can withdraw from the study at any time without providing a reason and without any consequences for their future treatment. The reason for withdrawal, if provided, is documented in the study records.

### Documentation

The study physician is responsible for ensuring that the study is conducted in accordance with the medical professional code, the Declaration of Helsinki and the study protocol, and that all data is correctly documented. All data collected during the study must be entered into the eCRF by authorized personnel, including data from participants excluded from the study.

The study center will maintain a patient identification list containing the participant number, full name, date of birth and date of inclusion. This list will remain at the study center upon study completion. In addition, the participation in the study including participant number, study start and end dates, will be documented in the medical record.

### Data management

All data entered by the study center will be managed and processed by the Clinical Trial Center (KKS) Dresden using the RedCAP software in accordance with data protection regulations. Should a study participant or their legal guardian requests data deletion, this will be carried out immediately.

The data will undergo range, validity and consistency checks. If necessary, queries wil be generated which authorized personnel will address. The study physician will review and resolve any discrepancies to ensure data accuracy. Upon completion of the study, the database will be closed only after all relevant data has been entered and queries resolved.

### Caseload planning

No prior studies in the literature have specifically examined the effect of guanfacine on AD in patients with ADHD. Therefore, there is no direct prior evidence regarding the effect of guanfacine on AD in ADHD patients. Indirect evidence comes from a meta-analysis reporting moderate effect sizes (Hedges’ g = 0.51) for guanfacine in reducing oppositional behaviors (24). Since the current study directly measures AD and targets a population with high baseline AD values due to non-response to stimulants, we assume medium to large effect sizes of Cohen's d = 0.65.

Sample size calculation was performed using G-Power program (http://www.gpower.hhu.de/). Assuning at least a medium effect sizes of Cohen's d = 0.50, a two-sided alpha error level of 5%, and a power of 0.90, a minimum of 34 participants is required. Accounting for a drop-out rate of approx. 15% the target sample size is *n* = 40 participants.

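### The stated power of 0.90 does not follow from 34 participants at d = 0.50: a paired t-test gives 0.81, and 0.87 even with all 40

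*Protocol article*

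**What the plan says.** The Caseload planning section gives two effect sizes. It first says "we assume medium to large effect sizes of Cohen's d = 0.65", reasoning from a meta-analytic Hedges' g of 0.51 for oppositional behaviour and from the high baseline dysregulation expected in this population. It then reports a G*Power calculation for "at least a medium effect sizes of Cohen's d = 0.50", with "a two-sided alpha error level of 5%, and a power of 0.90, a minimum of 34 participants is required". The last step reads "Accounting for a drop-out rate of approx. 15% the target sample size is" 40, which agrees with the Number of patients section.

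The Study design section describes a single-arm longitudinal study. The Data analysis section compares T1 with T2 by an ANOVA that it equates with a paired t-test, and it leaves drop-outs out. The Population for analysis section plans to analyse all 40 with multiple imputation where needed, and also the complete cases. The article states no T1–T2 correlation and does not say by which standard deviation d is scaled.

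**The concern.** The section prints effect size, alpha, sidedness, power and the resulting number, and the test is named elsewhere in the article. The result can therefore be checked directly, and it does not follow from the inputs. This is not a detail left to a fuller document.

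At stake is the error rate the design claims at its planning effect. A reader who trusts the figure will believe that a true change of d = 0.50 would be missed one time in ten, when with the planned number of completers it would be missed about one time in five. A non-significant result on the primary outcome (change in DADYS-EF) could then be taken as firmer evidence of no change than it is. With two effect sizes in one section, it also matters which of them, if either, supports 34.

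**Working it through.** **Inputs, all from Caseload planning unless noted**
- Effect size d = 0.50 for the calculation; d = 0.65 named as the expected effect
- Alpha 0.05, two-sided
- Power 0.90
- Minimum number 34; drop-out about 15%; target 40
- Test: paired t-test (Data analysis)
- Assumption, because the article does not say: d is the mean T1–T2 change divided by the SD of the change

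**Method.** Exact power of the paired t-test: noncentral t with n − 1 degrees of freedom and noncentrality d × √n, compared with the two-sided 5% critical value.

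**Step 1: the plan's own figures.** The drop-out step reproduces: 34 / (1 − 0.15) = 40. The step before it does not.

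| n | d × √n at d = 0.50 | Power |
|---|---|---|
| 33 | 0.50 × 5.745 = 2.872 | 0.795 |
| 34 | 0.50 × 5.831 = 2.915 | 0.808 |
| 40 | 0.50 × 6.325 = 3.162 | 0.869 |
| 43 | 0.50 × 6.557 = 3.279 | 0.893 |
| 44 | 0.50 × 6.633 = 3.317 | 0.900 |

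The smallest n for power 0.90 is 44. The smallest n for power 0.80 is 34.

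**Step 2: check by hand.** The normal approximation is n = ((z for alpha/2 + z for power) / d)².
- Power 0.90: ((1.960 + 1.282) / 0.50)² = 42.0, rounded up to 43
- Power 0.80: ((1.960 + 0.842) / 0.50)² = 31.4, rounded up to 32

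The exact t calculation adds one or two, giving 44 and 34. A repeated-measures ANOVA calculation (f = 0.25, correlation 0.5) also gives 44, with power 0.808 at n = 34.

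**Step 3: other readings that might give 34 at power 0.90.**

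| Reading | n for power 0.90 | Power at n = 34 |
|---|---|---|
| d = 0.65, two-sided | 27 | 0.957 |
| d = 0.51 (the cited g), two-sided | 43 | 0.823 |
| d = 0.50, one-sided 5% | 36 | 0.887 |

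None gives 34, and the one-sided reading contradicts the stated two-sided alpha.

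**Step 4: d scaled by the raw-score SD.** With equal SDs at T1 and T2, the effect on the change scale is d / √(2 × (1 − ρ)), where ρ is the T1–T2 correlation. For d = 0.50:

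| ρ | Effect on change scale | n for power 0.90 | Power at n = 34 |
|---|---|---|---|
| 0.3 | 0.423 | 61 | 0.667 |
| 0.4 | 0.456 | 53 | 0.733 |
| 0.5 | 0.500 | 44 | 0.808 |
| 0.6 | 0.559 | 36 | 0.886 |
| 0.7 | 0.645 | 28 | 0.955 |

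Power 0.90 at n = 34 requires an effect of 0.573 on the change scale, hence ρ of about 0.62: 0.50 / √(2 × 0.38) = 0.574.

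**Step 5: consequences.** With 34 completers the type II error at d = 0.50 is 1 − 0.808 = 0.192, against a claimed 0.10. Keeping 0.90 at d = 0.50 would need 44 completers, and 44 / 0.85 = 51.8, so 52 enrolled.

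**The case against.** The strongest counter-argument is that the article never defines d. If d = 0.50 is scaled by the raw-score SD, a T1–T2 correlation of about 0.62 would make 34 correct, and the meta-analytic g that anchors the effect is not described as a change-score effect. It stands that 44 is conditional on how d is defined. It does not rescue the printed statement, because no correlation appears anywhere and the answer is very sensitive to it (61 down to 28 participants for correlations of 0.3 to 0.7). A calculation resting on that value would have to state it.

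Three further points have some force. First, an expected effect of 0.65 beside a more cautious planning value of 0.50 is ordinary practice and no contradiction in itself. Second, the practical damage is limited: 0.81 is a conventional power, the power at the expected effect is 0.96, and no passage plans to read a null result as proof of no change. Third, the near-doubling of the type II error applies to 34 completers; with all 40 observed it would be 13%. However, 0.87 is what 40 fully observed pairs give. The Data analysis section leaves drop-outs out, so at the planned 15% drop-out the complete-case figure is 0.81.

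That the authors used 0.80 in the software is suggested by the exact match at 34, but it remains an inference.

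**Conclusion.** The statement is wrong as written. For the planned paired comparison at d = 0.50, two-sided 5%, power is 0.81 with 34 completers and 0.87 with all 40. Power 0.90 needs 44, ten more than stated. The type II error at the planning effect is 19%, about twice the 10% claimed.

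These figures assume that d is the mean change over the SD of the change and that 15% drop out. No alternative supported by the text gives 34; the only route to it needs an unstated correlation of about 0.62. The finding concerns the power claimed at d = 0.50. It does not show that the study is too small for its expected effect of 0.65.

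**What to change.** Keep N = 40 and correct the sentence in Caseload planning. Suggested wording:

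> Cohen's d is the mean T1–T2 change divided by the standard deviation of the change. With a paired t-test at two-sided alpha 5%, 34 completers give power 0.81 for d = 0.50; power 0.90 is reached at d = 0.57. For the expected d = 0.65 the power is 0.96. With 15% drop-out, 40 participants are enrolled.

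The sentence on d = 0.65 may be dropped instead, so that one effect size clearly supports the sample size. If the original calculation used d on the raw-score SD, give the assumed T1–T2 correlation and its justification, and show the power over a range of correlations.

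This costs a change of wording and a less favourable stated power, with no extra patients. Only if the sponsor wants to keep 0.90 at d = 0.50 does the sample size change: 44 completers, about 52 enrolled, 12 more than planned.

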### Statistical methods

#### Outcome measures

Behavioral parameters will be assessed using self-report and parent-report rating scales at time point T1 (before guanfacine) and T2 (9 or 10 weeks after inclusion, guanfacine continued).

#### Population for analysis

The study population consist of participants measured longitudinally at two time points. Data from all *n* = 40 participants will be analyzed, including multiple imputation for missing data where necessary, and complete case analysis will be performed.

#### Data analysis

Differences between T1 and T2 will be analyzed using one-way analysis of variance (ANOVA), equivalent to a paired Student's *t*-test under normal distribution assumptions. Drop-out cases will not be included, but described in detail.

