## Methods and analysis

### Study design

This is a non-interventional test in accordance with German Arzneimittelgesetz (AMG) §4(23). The design is multicentric, prospective, open, single-arm, longitudinal.

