### Primary objective of the study

Change in DADYS-EF (Affective Dysregulation Questionnaire) between Visit 1 and Visit 2.

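### The primary test is named as a one-way ANOVA and called equivalent to a paired t-test, which is true only of a repeated-measures ANOVA; the wording should name the paired analysis (minor)

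*Protocol article*

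**What the plan says.** The Data analysis section is the only place in the protocol article that names the test: "Differences between T1 and T2 will be analyzed using one-way analysis of variance (ANOVA), equivalent to a paired" Student's t-test, with the qualifier that normality is assumed. The words repeated-measures and within-subject do not appear.

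Other sections fix the structure of the data:

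- Study design: "The design is multicentric, prospective, open, single-arm, longitudinal".
- Primary objective of the study: "Change in DADYS-EF (Affective Dysregulation Questionnaire) between Visit 1 and Visit 2".
- Population for analysis: the study population is made up of "participants measured longitudinally at two time points".
- Caseload planning: the sample size rests on "at least a medium effect sizes of Cohen's d = 0.50", "a two-sided alpha error level of 5"%, and power 0.90. It arrives at 34 participants, raised to 40 for drop-out. The section does not name the test behind the calculation, does not say whether d is standardised by the SD of the scores or of the change, and gives no T1–T2 correlation.

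**The concern.** With two levels, an ordinary one-way ANOVA gives F equal to the square of the unpaired t statistic. It treats the T1 and T2 scores as if they came from different children and leaves the between-child variance in the error term. Only the repeated-measures form removes that variance and gives F equal to the square of the paired t statistic. That identity is algebraic, so the qualifier about normality does not make the ordinary form equivalent.

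The sentence therefore names one procedure and describes another. It is a statement about the primary test that is incorrect as worded, so it is more than detail left to an analysis plan. It also appears to govern every secondary change score, since no other test is named. What is at stake is limited to the case in which someone follows the label and not the description: standard errors too large, confidence intervals too wide, and a test that rejects too rarely.

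**Working it through.** **Inputs.** From Caseload planning: d = 0.50, two-sided alpha 0.05, n = 34. Assumptions: d is the paired effect size dz (mean change divided by the SD of the change), the T1 and T2 variances are equal, and the T1–T2 correlation ρ is 0, 0.3, 0.5 or 0.7. The article gives no value of ρ.

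**Step 1: the plan's own figure.** The power of a paired t-test comes from the noncentral t distribution with n − 1 degrees of freedom and noncentrality dz·√n. With n = 34 and dz = 0.50, the noncentrality is 0.50 × √34 = 2.915, the critical value is t(0.975; 33) = 2.035, and power is 0.808. The stated inputs with power 0.90 need 44 pairs, not 34; 34 is the paired answer for power 0.80. This discrepancy is a separate sample-size issue and does not arise from the ANOVA wording. It is shown here only because 0.81 is the reference for the comparison below.

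**Step 2: which ANOVA equals which t-test.** On one simulated dataset of 34 pairs:

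| Analysis | Statistic | Equals | p |
|---|---|---|---|
| Repeated-measures ANOVA, time within child | F = 5.345 | paired t² = 2.312² | 0.027 |
| Ordinary one-way ANOVA | F = 2.934 | unpaired t² | 0.091 |

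The same data fall on either side of 5% depending on which test is meant.

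**Step 3: standard errors.** With common SD σ:

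- unpaired: SE = σ·√(2/n)
- paired: SE = σ·√(2(1 − ρ)/n)
- ratio, unpaired to paired = 1/√(1 − ρ): 1.00, 1.20, 1.41 and 1.83 at ρ = 0, 0.3, 0.5 and 0.7.

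**Step 4: cost of the literal reading.** For a fixed dz the raw difference is dz·σ·√(2(1 − ρ)). Simulated results with n = 34 and dz = 0.50:

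| ρ (assumed) | Power, paired | Power, ordinary one-way ANOVA | Type I error, ordinary one-way ANOVA |
|---|---|---|---|
| 0 | 0.81 | 0.82 | 5% |
| 0.3 | 0.81 | 0.70 | about 2% |
| 0.5 | 0.81 | 0.54 | about 0.7% |
| 0.7 | 0.81 | 0.25 | about 0.07% |

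Hand check at ρ = 0.5: the ordinary ANOVA rejects when the correctly scaled statistic exceeds about t(0.975; 66)/√(1 − ρ) = 1.997/0.707 = 2.824. Power is then roughly Φ(2.915 − 2.824) = Φ(0.091) = 0.54, as simulated.

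**Step 5: if d is the raw standardised difference.** With d = 0.50 on the scale of the scores and n = 34, the ordinary ANOVA has power 0.53 to 0.56 for ρ from 0 to 0.8. The paired test has 0.52, 0.67, 0.81, 0.96 and 0.99 at ρ = 0, 0.3, 0.5, 0.7 and 0.8. The size of the loss changes, but not its direction once ρ is clearly above zero.

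**The case against.** The strongest reply is that the sentence defines itself. The term one-way only counts factors, and a one-way repeated-measures ANOVA with two time points is exactly a paired t-test, which is what the sentence claims. The single-arm longitudinal design, the within-child primary objective and the absence of any between-child factor leave no other sensible reading. The sample size agrees: 34 at d = 0.50 is a paired result (power 0.81), whereas an independent-groups comparison would need 64 per group for 80% power and 86 per group for 90%. The article is also condensed, and an analysis plan may well state the within-subject error term.

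Most of this stands. A reader might infer that the trial will ignore the pairing and lose much of its power. The document does not support that inference: the equivalence clause is part of what is written, and on the paired reading nothing is lost at any correlation. Even on the literal reading, the error at positive correlation is conservative and does not raise the false-positive rate.

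What does not fall away is that the method as named is not, in ordinary usage, the method described. The only sentence that fixes the primary test should not need the reader to work out which half governs.

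**Conclusion.** The label is incorrect as worded, and a paired analysis is very probably intended. On that reading the consequence is nil. The losses shown (power from 0.81 to about 0.70, 0.54 or 0.25, with type I error of about 2%, 0.7% or 0.07%) are the cost of running the named method literally and are not a forecast for this trial. They rest on three assumptions: 34 completers, d = 0.50 as a paired effect size, and T1–T2 correlations of 0.3, 0.5 or 0.7. The loss vanishes at zero correlation. Some positive correlation is to be expected for the same parent-rated scale on the same child about ten weeks apart, but the article gives no value. Severity: minor. The gap between 0.81 and the stated power of 0.90 should be dealt with under sample size and adds no weight here.

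**What to change.** Replace the sentence in Data analysis with: *The mean T1–T2 change in DADYS-EF will be tested with a two-sided paired t-test (equivalently, a repeated-measures ANOVA with time as the within-subject factor) and reported with its 95% CI.* State that the secondary change scores are analysed in the same way, and carry the same wording into the statistical analysis plan if there is one. The cost is one sentence; data collection, visits and sample size are unaffected.

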## Discussion

Based on clinical experience, we expect the results of this study to support our hypothesis.

To the best of our knowledge, this is the first study to investigate the effects of guanfacine on AD in ADHD. This strength helps to counterbalance potential limitations, such as the non-blinded, single-arm study design.

If the hypothesis is confirmed, the clinical implications for managing AD in children and adolescents could be substantial. Compared to antipsychotics, the primary pharmacological alternative, guanfacine is better tolerated, with a more favorable side-effect profile. Therefore, guanfacine would not only be an approved pharmacological treatment of AD in ADHD, but could also offer potential benefits in the treatment of AD independently of coexisting ADHD.

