### Inclusion criteria

•Male and female patients aged 6–17 years.•Diagnoses F90.0 (ADHD) or F90.1 (hyperkinetic disorder of social behavior).•Patients have not responded adequately to stimulants or these are not suitable for clinical reasons; switching to guanfacine is clinically indicated and regularly planned.•Patients show clinical symptoms of affective dysregulation.•IQ is at least 70.•Written informed consent from the participating patients and their legal guardians.

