## Ethics and dissemination

### Need to conduct the clinical study

AD has a significant impact on the mental health of children, adolescents, and adults. In children and adolescents, the treatment of AD is a critical focus of psychotherapeutic and milieu-therapeutic interventions. However, in many cases, these approaches fail to achieve sufficient improvement, underscoring a significant need for additional treatment options, particularly pharmacological strategies. Currently, no pharmacological treatment is approved in Germany for the treatment of AD. Unofficial clinical case reports have suggested that guanfacine may be effective in the treatment of AD in children and adolescents with ADHD. As described above, there is supporting evidence in the literature indicating the potential efficacy of guanfacine in this context. Guanfacine is an already approved medication for treating the core symptoms of ADHD in children and adolescents. This study aims to address a critical gap by investigating, for the first time, whether guanfacine can also effectively reduce symptoms of affective dysregulation in addition to treating the core symptoms of ADHD. If successful, this study could offer significant advancements in the treatment of AD in children and adolescents and provide a much-needed pharmacological option for this challenging condition.

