### Benefit-risk assessment

Ethical research projects must address new and relevant research questions while minimizing the burden on study participants in relation to the potential benefits. In studies involving children and adolescents, the need for special protection is a particularly important consideration. The study design described here has been carefully developed to ensure the research question is answered effectively while prioritizing participant safety and minimizing risks.

The research question—whether guanfacine has a beneficial effect on AD in an ADHD population—offers significant potential benefit. The question is novel and has not been answered despite preliminary indications from the existing literature. AD is associated with substantial distress in children and adolescents; and identifying of an additional treatment option for severe cases, particularly in the context of ADHD and potentially in other clinical constellations, would hold considerable clinical value.

Participation in the study involves no plausible or significant risks. The study will accompany regular clinical dosing of guanfacine in children and adolescents with ADHD by conducting psychometric assessments before and after treatment initiation. Data collection is limited to psychometric evaluations, completed by patients and their primary caregivers using standardized rating questionnaires. Consequently, the study imposes minimal burdens, as no study procedures are invasive in nature.

From a benefit-risk perspective, the potential benefits of this study clearly outweigh the risks. The study offers meaningful opportunities to gain clinically relevant insights while ensuring participant safety and minimizing inconvenience.

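### The Discussion reads a before-after change in an open, single-arm study as evidence that guanfacine treats affective dysregulation (AD); the planned test cannot show that

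*Protocol article*

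**What the plan says.** - **Design (Study design):** "The design is multicentric, prospective, open, single-arm, longitudinal". The study is non-interventional.
- **Primary objective:** "Change in DADYS-EF (Affective Dysregulation Questionnaire) between Visit 1 and Visit 2". Read with the Aims and the visit lists, DADYS-EF is the parent-report version.
- **Test (Data analysis):** T1 against T2 by a one-way ANOVA, described as "equivalent to a paired Student's *t*-test under normal distribution assumptions". No comparator and no benchmark for change without the drug is stated.
- **Selection (Inclusion criteria):** "Patients show clinical symptoms of affective dysregulation". Under the section on routine guanfacine treatment, the treating physician judges this once the treatment decision has been made and before T1. Caseload planning expects high baseline AD.
- **Stated aim (Aims of the study):** cautious. It asks whether AD changed, as an epidemiological observation.
- **Wider question (Benefit-risk assessment):** "whether guanfacine has a beneficial effect on AD in an ADHD population". Research question and Need to conduct the clinical study are likewise worded as questions of efficacy.
- **Reading of a positive result (Discussion):** if the hypothesis is confirmed, "guanfacine would not only be an approved pharmacological treatment of AD in ADHD", with potential benefit for AD apart from ADHD. On being the first such study: "This strength helps to counterbalance potential limitations, such as the non-blinded, single-arm study design".

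**The concern.** The test can reject only the statement that the mean change is zero. To move from there to the statement that guanfacine works for AD, one must assume that without guanfacine the mean change would have been zero. Nothing in the design supports that assumption, and several features speak against it:

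- Parents rate the outcome and know that a new drug has been started.
- About ten weeks pass between the ratings (T2 is at day 70).
- Patients may be in outpatient, day-care or inpatient treatment, and the article itself describes psychotherapeutic and milieu-therapeutic work as directed at AD.
- Patients enter because they show AD symptoms when a change of treatment has been decided.

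At stake is the meaning of the primary result. A reader of the Discussion would take a significant paired test as support for using guanfacine against AD, even in children without ADHD, whom the study does not observe.

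**Working it through.** **1. The plan's own figure.** Caseload planning gives 34 participants for d = 0.50, two-sided 5%, power 0.90, and 34/(1 − 0.15) = 40 with drop-out. For a paired t-test, power is P(|t′| > t(0.975; n − 1)), where t′ is noncentral t with n − 1 degrees of freedom and noncentrality dz·√n (dz = mean change divided by the SD of the differences). At n = 34 and dz = 0.50 the noncentrality is 0.50 × 5.831 = 2.915 and the power is 0.81; 0.90 needs 44. The figure of 34 therefore does not reproduce. That is a separate matter and does not affect this point. I use n = 34 as the plan's number of completers.

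**2. What makes the test significant.** The observed change must exceed t(0.975; 33)/√34 = 2.035/5.831 = 0.35 SD of the differences (0.32 at n = 40), whatever its cause.

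**3. Probability of significance with no drug effect.** The same formula, with dz now the change from non-drug causes. The dz values are assumptions; the document gives none.

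| Assumed non-drug dz | Noncentrality at n = 34 | P(p < 0.05), n = 34 | P(p < 0.05), n = 40 |
|---|---|---|---|
| 0 | 0 | 5% | 5% |
| 0.2 | 1.166 | 21% | 23% |
| 0.3 | 1.749 | 40% | 46% |

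A larger sample makes this worse: it detects a non-drug change more reliably.

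**4. Can the share from regression to the mean be fixed?** Selection is by a clinical judgement S made before T1, not by a DADYS-EF cut-off. In a bivariate-normal model the expected shift, in SDs of the score, is (corr(S,T1) − corr(S,T2)) × λ(q), where q is the selected share, c = Φ⁻¹(1 − q) and λ(q) = φ(c)/q.

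- If S correlates equally with T1 and T2, the shift is 0 and the rejection rate stays at 5%.
- If the correlations are 0.7 and 0.6, q = 50% (λ = 0.798) and corr(T1,T2) = 0.7, the shift is 0.1 × 0.798 = 0.08. The variance of the difference after selection is 2(1 − 0.7) − 0.1² × 0.798² = 0.594, so dz = 0.08/0.77 = 0.10 and the rejection rate is 9%.
- More extreme assumptions (correlations 0.7 and 0.5, q = 10%) reach 75%.

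The document supplies neither the correlations nor the selected share, so this component cannot be sized.

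**5. Text against design.** The Inclusion criteria require F90.0 or F90.1, so there are no data on AD without ADHD. Being first adds no information on what would have happened without the drug, so it cannot reduce bias from a missing control.

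**The case against.** **The design is disclosed and legitimate.** The study is declared non-interventional, open and single-arm. The Aims section is cautious, the primary objective is only a change, and the Discussion names the design as a limitation. No endpoint or analysis rule makes a causal claim. All of this stands, and it is why the point concerns the stated conclusion and not the design. It does not rescue the Discussion, which names the limitation and then discounts it.

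**Regression to the mean may be small.** Selection precedes T1, rests on a physician's judgement, and concerns patients with a long treatment history, whose AD may be persistently high. This also stands. A reader might infer that regression to the mean alone would make the result significant, for instance by modelling entry as a cut-off on the T1 score. The article sets no such cut-off, so that inference is not supported.

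**Approval.** A reader might see a contradiction with Need to conduct the clinical study: "Currently, no pharmacological treatment is approved in Germany for the treatment of AD". That sentence describes the present. The Discussion is conditional and may only mean that a drug already approved for ADHD would also act on AD. This is loose wording, not a firm conflict, but it should go because no result of this study could confer approval.

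**Tolerability.** A reader might object that the Discussion claims better tolerability than antipsychotics while the visits list no safety outcome. The remark is background, not a planned conclusion of the study, and is no fault here.

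**Hedging.** The benefit apart from ADHD is stated only as a possibility. Even so, it is made conditional on a result that cannot bear on it.

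**Conclusion.** The point holds as a fault of inference. The nominal 5% applies to the hypothesis of no change. Under the hypothesis of no guanfacine effect, the chance of a significant result is 5% only if all non-drug change is zero; it is 21% or 40% if that change is 0.2 or 0.3 SD of the differences at n = 34. These values are assumptions that show sensitivity, not estimates for this study. The logical fault does not depend on them, because without a comparator or benchmark the study cannot separate drug from non-drug change. The extension to AD without ADHD lies outside the population studied. The documents do not support saying that a significant result would be spurious, or that the single-arm design is unsuitable for describing change under routine care.

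**What to change.** 1. In the Discussion, replace the text on confirmation and its implications with, for example: *A significant result will be reported as a pre-post change in DADYS-EF over the course of routine guanfacine treatment, with its 95% confidence interval. It will not be taken to show that guanfacine caused the change. Parent expectancy, natural course, concurrent care and regression to the mean are alternative explanations that this design cannot exclude.*
2. Delete the sentence saying that novelty helps to offset the design, the wording about an approved treatment of AD, and the inference to AD apart from ADHD.
3. Bring the efficacy wording in Need to conduct the clinical study and Benefit-risk assessment into line with the observational aim in Aims of the study.

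The cost is wording only. The conclusion becomes more modest; endpoint, visits, sample and analysis do not change. A second pre-treatment questionnaire is not proposed: treatment decision and initiation are only 2-3 weeks apart, and consent falls within that time, so the added interval could not estimate natural course over 70 days or expectancy after treatment starts.
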